### Intervention

An ophthalmologist will examine all patients to ensure normal visual function one day before the surgery. The patients will also undergo intraoperative neurophysiological monitoring using electrodes placed subcutaneously or in a corkscrew, including FVEPs and electroretinography (ERG) monitoring (to ascertain efficient delivery of retinal light stimulation).

The corkscrew electrodes for FVEPs will be located in the occipital zero (OZ) (4 cm above the occipital trochanter), O1 (4 cm left lateral to the OZ), O2 (4 cm right lateral to the OZ), frontal zero (FZ) (midfrontal area, 10–12 cm above the nose), and 2 ground electrodes. Electrodes for ERG will be placed 2 cm from the lateral canthus of the patient’s eyes (Fig. 3). FVEP stimulation, data recording, and storage will be performed using the Medtronic NimEclipse neuromonitoring system, which provides goggles with 6 embedded light-emitting diode (LED) bulbs. The specific parameters will be as follows: white light source high-intensity LED, 1.1 Hz stimulation frequency, 5000 to 10,000 lx laser emission, smoothing bandpass 20 to 100 Hz, and 1 to 100 Hz filter bandpass [21–23]. Each pulse stimulation will last 10 ms. The same experienced neuroelectrophysiologist will monitor intraoperative FVEPs for all procedures. We named the vertical distance between N75 and P100 the N75-P100 amplitude and the vertical distance between P100 and N145 the P100-N145 amplitude and defined P100 as the latency of FVEPs in our study. We will measure the baseline amplitude and latency of FVEPs 30 min after anesthesia induction under TIVA in both groups, which will be marked as N75-P100 (TIVA), P100-N145 (TIVA), and P100 (TIVA). Then, anesthesia maintenance with the HD group or LD group will be implemented according to the randomization results. We will measure the amplitude and latency of FVEPs 60 min after anesthesia induction in LD or HD group, which will be accordingly marked as N75-P100 (LD), P100-N145 (LD), and P100 (LD) vs N75-P100 (HD), P100-N145 (HD), and P100 (HD). At each chosen time point, we will measure the N75-P100 amplitude, P100-N145 amplitude, and P100 latency 3 times and record the average of the measurements.

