### Remedy

If the FVEPs fail to record, neurophysiologists will check the stimulating apparatus and conditions, such as the stimulus intensity of light, intervals, and waves of ERG, to ensure light conduction and ascertain efficient delivery of retinal light stimulation [17]. The anaesthesiologists will check physiological parameters such as blood pressure, body temperature, and positioning. If an ideal FVEP waveform cannot be obtained after excluding all the above reasons, the surgeon will decide whether to continue the operation. Finally, if the FVEPs fail to record or the surgery is suspended, the patients will remain in the study, but the event will be recorded on the case report form.

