### Study endpoints

FVEP stimulation, data recording, and storage will all be performed using the Medtronic NimEclipse neuromonitoring system. The same experienced neuroelectrophysiologist will monitor intraoperative FVEPs for all procedures.

The primary endpoint of this study is the N75-P100 amplitude at 60 min after the induction of anesthesia, which is defined as the mean N75-P100 amplitude on O1, O2, and Oz leads in both eyes.

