### Sample size calculation

We used PASS 15 to calculate the sample size for this study. According to the pre-experiment results, at 60 min after induction of anesthesia, the amplitudes of the LD group and HD group were 3.43 ± 0.78 μV and 2.37 ± 0.80 μV, respectively. According to the results of other studies, the superiority margin was defined as 20% of the N75-P100 amplitude in the HD group [6]. According to *α* = 0.025 and *β* = 0.2, a sample size of 63 cases can provide a superiority margin of 20% higher amplitude in the LD group than in the HD group. We conservatively set the dropout rate at 10% on the basis of actual 1.7% in our previous study, the sample size should be a total of 70 persons will be enrolled, and 35 patients in each group.

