### Statistical analysis

All data analyses will be performed on both a per-protocol (PP) and intention-to-treat (ITT) basis. The intent-to-treat population will include all subjects randomized to receive HD or LD anesthesia maintenance, and the completed FVEP data will be collected. The per-protocol population will include all subjects in the ITT population not identified as protocol violators (i.e., change in the anesthesia strategy after the trial initiates). These protocol violations will be shown in a listing. Subjects who do not obtain available FVEP data or abandon the study for various reasons will be considered to have failed HD/LD and will be excluded from any form of analysis. For the missing data, the last observation and the worst-case imputation scenarios will be used as the main interpolation method.

The statistical analysis will be performed by an independent statistician using SPSS V.25.0 (Somers, NY, USA). Histograms and the Shapiro‒Wilk test will be used to assess the normality of the data distribution. For the statistical description, the continuous variables will be presented as the mean (standard deviation, SD) for normally distributed data or median (interquartile range, IQR) for skewed distributions. Categorical variables will be reported as counts and percentages, and the relative risk with its 95% confidence interval (CI) will be calculated. The absolute standard deviation (ASD) will be determined to identify any imbalance in baseline characteristics.

The primary outcome (N75-P100 amplitude of FVEPs recorded 1 h after induction) will be analyzed using a superiority test. According to the results of other studies, the superiority margin was defined as 20% of the N75-P100 amplitude in the HD group [6].For secondary outcomes, *χ*^2^ tests or Fisher’s exact tests will be performed for categorical variables including N75-P100 amplitude decline rate, P100-N145 amplitude decline rate, rate of prolongation of P100 latency, success rate of FVEP monitoring, FVEP stacking satisfaction, adverse events related to FVEP monitoring, and recovery quality. Anaesthetic and vasoactive drug agent consumption will be analyzed using independent samples *t*-tests for normally distributed variables and Wilcoxon sum tests for variables with skewed distributions. The study will terminate after all the data for the last patient are collected.

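### The protocol gives incompatible rules for a missing 60-minute FVEP amplitude, and one of them, last observation, can only carry forward the pre-intervention TIVA baseline

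*Protocol article*

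**What the plan says.** All places are in the Protocol article.

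- **Measurement times (Intervention).** "We will measure the baseline amplitude and latency of FVEPs 30 min after anesthesia induction under TIVA in both groups". The randomized regimen follows: "Then, anesthesia maintenance with the HD group or LD group will be implemented according to the randomization results". The next scheduled reading is at 60 minutes.
- **Primary endpoint (Study endpoints).** "The primary endpoint of this study is the N75-P100 amplitude at 60 min after the induction of anesthesia", averaged over three leads and both eyes. The decline and prolongation rates compare this reading with the TIVA reading.
- **Failed recordings (Remedy).** "if the FVEPs fail to record or the surgery is suspended, the patients will remain in the study", with the event noted on the case report form.
- **Exclusion (Statistical analysis).** Patients without available FVEP data, or who abandon the study, "will be considered to have failed HD/LD and will be excluded from any form of analysis".
- **Imputation (Statistical analysis, next sentence).** "the last observation and the worst-case imputation scenarios will be used as the main interpolation method". No order is given between the two methods, nor any split by variable, and worst case is not defined for an amplitude.

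**The concern.** A patient may have a valid TIVA baseline and no usable 60-minute amplitude. The text offers four treatments for that patient: retain, exclude, impute by last observation, or impute by worst case. They lead to different primary results, so the primary analysis is not determined once one such value is missing.

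Last observation has a further problem. Its only scheduled source is a reading under a different anaesthetic, before the regimen under test began. It does not extrapolate a post-intervention course; it asserts that the regimen did nothing. The Background section says that anaesthetics can make FVEP extraction fail, so a lost waveform may itself be a regimen effect, and this rule would record it as no effect.

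The exclusion sentence also collides with a secondary endpoint. The monitoring success rate uses all monitored eyes as its denominator. A patient whose two eyes both fail would leave numerator and denominator if excluded from every analysis.

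**Working it through.** **Inputs**

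- Sample size calculation: "the amplitudes of the LD group and HD group were 3.43 ± 0.78 μV and 2.37 ± 0.80 μV, respectively". The planned difference is 3.43 − 2.37 = 1.06 µV.
- Margin: "the superiority margin was defined as 20% of the N75-P100 amplitude in the HD group", which is 0.20 × 2.37 = 0.474 µV.
- Planned excess over the margin: 1.06 − 0.474 = 0.586 µV.
- One-sided α = 0.025, power 80%, 35 per arm, planned dropout 10%, dropout in the previous study 1.7%.
- The TIVA amplitude B is not given. Assumption: 3.0–4.5 µV, SD 0.80, the same in both arms because it precedes the regimens.

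**The plan's own figure.** n per arm = 2 × (1.960 + 0.842)² × SD² / 0.586². With SD 0.80 this gives 30 per arm (60 in total), or 31 per arm (62) with the noncentral t. With the pooled SD 0.79 it gives 58 and 60. The stated 63 is within one patient of the largest of these. The dropout step is exact: 63 / 0.90 = 70.

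**What last observation imputes.** Setting the 60-minute value equal to the TIVA value:

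- amplitude decline = (TIVA − TIVA) / TIVA = 0%
- latency prolongation = (TIVA − TIVA) / TIVA = 0%

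**Equal missing fraction f in both arms**, with observed patients at the planned means:

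[(1 − f) × 3.43 + f × B] − [(1 − f) × 2.37 + f × B] = (1 − f) × 1.06

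B cancels. At f = 10% the difference is 0.954 µV; at f = 1.7% it is 1.042 µV.

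**10% missing in HD only.** HD mean = 0.9 × 2.37 + 0.1 × B = 2.433 µV (B = 3.0) to 2.583 µV (B = 4.5). The rise over 2.37 is 0.063–0.213 µV. Divided by 0.586, that is 11–36%. The difference falls to 0.997–0.847 µV.

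**10% missing in LD only.** LD mean = 0.9 × 3.43 + 0.1 × B = 3.387–3.537 µV. The difference is 1.017–1.167 µV. The direction turns at B = 3.43: below it the arms move together, above it they move apart.

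**Power** (normal approximation, 35 per arm, margin fixed at 0.474):

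- Arm variance = (1 − f) × SD² + f × 0.80² + f(1 − f) × (B − arm mean)²
- Power = Φ[(difference − 0.474) / √((sum of the two arm variances) / 35) − 1.96]

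| Scenario | Difference (µV), B = 3.0 / 4.5 | Power, B = 3.0 / 4.5 |
|---|---|---|
| Nothing missing | 1.060 | 0.873 |
| 1.7% carried forward, both arms | 1.042 / 1.042 | 0.85 / 0.83 |
| 10% carried forward, both arms | 0.954 / 0.954 | 0.70 / 0.57 |
| 10% carried forward, HD only | 0.997 / 0.847 | 0.78 / 0.40 |
| 10% carried forward, LD only | 1.017 / 1.167 | 0.81 / 0.94 |
| 10% left out of both arms, missing at random | 1.060 | 0.837 |

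**The case against.** **The exclusion sentence may come first.** A patient whose waveform is lost under desflurane may be one without available FVEP data, and would then be dropped, not imputed. The definition of the ITT set, which mentions completed FVEP data, points the same way. This stands as a possible reading, so a reader should not infer that such a patient will certainly be scored as unaffected. It does not settle the matter: a patient with a TIVA baseline, or with one eye recorded, has some FVEP data.

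**Remaining in the study is not the same as being analysed.** True, but exclusion from every analysis then leaves nothing for the retained patient to contribute, including to the success rate.

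**Last observation is not the only main method, and not always baseline carry-forward.** Worst case is named beside it. The rule covers missing data generally, and for the agitation and sedation scores, rated at four times after awakening, a post-intervention value does exist. FVEPs are monitored during surgery and Fig. 1 is not shown, so an unscheduled reading between 30 and 60 minutes is conceivable; the text schedules none.

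**Missingness may be rare.** The previous study had 1.7% dropout and 100% monitoring success. At 1.7% the effect is small and power stays above 80% under the assumptions used here. That study compared sevoflurane at 0.5 MAC with TIVA, however, so it does not inform failure under high-concentration desflurane. The documents give no figure for that.

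**Conclusion.** The protocol's rules for a missing 60-minute amplitude are incompatible, and one named main method imputes no regimen effect because its only scheduled source is the pre-intervention baseline. The effect is minor at 1.7% missing and material at 10% or when missingness differs between arms. The sizes rest on the assumed TIVA amplitude of 3.0–4.5 µV and on observed patients having the planned means.

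Three stronger readings are tempting and are not supported:

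- **That carry-forward always pulls the arms together, and so is conservative.** This fails when LD values are missing and the baseline exceeds 3.43 µV.
- **That worst case gives the opposite value.** Worst case is undefined. If it means unfavourable to LD and favourable to HD, a missing HD value is imputed high, in the same direction as a high baseline.
- **That 51–77% of the planned excess is at stake.** That figure is the gap between carry-forward and scoring 10% of HD as 0 µV: 0.1 × B = 0.30–0.45 µV, over 0.586. The protocol has no 0 µV rule. Against the planned HD mean the shift is 11–36%.

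**What to change.** 1. Reconcile the Remedy and Statistical analysis sections. Keep all randomized patients in the ITT set and delete the exclusion from every analysis.
2. Do not carry the TIVA baseline forward for the 60-minute FVEP outcomes (amplitudes, decline rates, latency prolongation).
3. Name one primary rule for a missing 60-minute amplitude before unblinding, for example multiple imputation within arm using the TIVA baseline. This assumes missingness at random given arm and baseline, so it needs the sensitivity analyses below.
4. Define worst case as unfavourable to LD and favourable to HD, and label it a sensitivity analysis.
5. Report waveforms that cannot be elicited under the existing success-rate endpoint, with all monitored eyes in the denominator. Scoring them as 0 µV changes the estimand and would widen the difference in favour of LD if failures concentrate in HD. It therefore belongs among the sensitivity analyses.

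The cost is revised analysis wording and a little more analysis work. No change to recruitment or measurement is needed.

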The secondary endpoints are as follows:N75-P100 amplitude decline rate compared to baseline measured under TIVA, calculated by the formula $$\frac{\left[N75-P100\left(TIVA\right)-N75-P100\left(HD\right)\right]}{\left[N75-P100\left(TIVA\right)\right]}\times100\%$$ or $$\frac{\left[N75-P100\left(TIVA\right)-N75-P100\left(LD\right)\right]}{\left[N75-P100\left(TIVA\right)\right]}\times100\%$$. N75-P100 (TIVA) will be measured 30 min after anesthesia induction under TIVA in both groups. N75-P100 (HD) or N75-P100 (LD) will be measured 60 min after anesthesia induction in HD or LD group.P100-N145 amplitude decline rate compared to baseline measured under TIVA, calculated by the formula $$\frac{\left[P100-N145\left(TIVA\right)-P100-N145\left(HD\right)\right]}{\left[P100-N145\left(TIVA\right)\right]}\times100\%$$ or $$\frac{\left[P100-N145\left(TIVA\right)-P100-N145\left(LD\right)\right]}{\left[P100-N145\left(TIVA\right)\right]}\times100\%$$. P100-N145 (TIVA) will be measured 30 min after anesthesia induction under TIVA in both groups. P100-N145 (HD) or P100-N145 (LD) will be measured 60 min after anesthesia induction in HD or LD group.Rate of prolongation of P100 latency compared to TIVA baseline measurements, calculated by the formula $$\frac{\left[P100\left(HD\right)-P100\left(TIVA\right)\right]}{\left[P100\left(TIVA\right)\right]}\times100\%$$ or $$\frac{\left[P100\left(LD\right)-P100\left(TIVA\right)\right]}{\left[P100\left(TIVA\right)\right]}\times100\%$$. P100 (TIVA) will be measured 30 min after anesthesia induction under TIVA in both groups. P100 (HD) or P100 (LD) will be measured 60 min after anesthesia induction in HD or LD group.The success rate of FVEP monitoring is defined as the ratio of the number of eyes with a satisfactory waveform to the number of all monitored eyes.FVEP stacking satisfaction will be assessed by electrophysiologists. A satisfactory waveform that could be evoked no more than three times will be considered satisfactory.Intraoperative anesthetic and vasoactive drug dosage, including anesthetics (i.e., sufentanil, remifentanil, propofol, rocuronium) and vasoactive agents (i.e., atropine, ephedrine, noradrenaline, phenylephrine, urapidil)Recovery quality:Respiratory recovery time is defined as the time from the cessation of anesthesia to the patient’s spontaneous breathing.Eye-opening time is the time from anesthesia cessation to when the patient can be called to open their eyes.Extubation time is defined as the time from the cessation of anesthesia to the removal of the patient’s tracheal catheter.Post-extubation agitation score. Ratings will be performed immediately after awakening and 15, 30, and 60 min after awakening: 1 point—restful sleep; 2 points—awake and calm; 3 points—irritability or irritability or crying; 4 points—difficulty to comfort or uncontrollable crying; 5 points—unable to be quiet or confused or delirium.Post-extubation sedation score. Ramsay sedation scale will be administered to the patients immediately after awakening and at 15, 30, and 60 min after awakening: 1 point—awake but anxious and restless; 2 points—cooperation, orientation, quiet; 3 points—drowsiness and response to commands; 4 points—drowsiness, rapid response to tapping eyebrow or loud auditory stimuli; 5 points—lethargy, slow response to tapping eyebrow or loud auditory stimuli; 6 points—drowsiness, no response at all. Scores 2–4 indicate satisfactory sedation and 5 to 6 excessive sedation.

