A 1-sided *P* value of 0.025 will be considered statistically significant for the primary outcome. If the confidence interval for mean differences of N75-P100 amplitude between LD and HD groups lied above the lower limit of *δ* with *P* < 0.025, we defined LD group will be superior to HD group. While all *P* values will be 2-sided with a significant level of 0.05 for the comparisons of N75-P100 amplitude decline rate, P100-N145 amplitude decline rate, rate of prolongation of P100 latency, success rate of FVEP monitoring, FVEP stacking satisfaction, anaesthetic and vasoactive drug agent consumption, and adverse events related to FVEP monitoring or recovery quality between the group LD and HD.

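### The primary comparison of 60-minute N75-P100 amplitude has no term for the TIVA baseline amplitude, which gives up precision and protection against chance imbalance

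*Protocol article*

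**What the plan says.** All references are to the protocol article.

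- **Endpoint (Study endpoints).** "The primary endpoint of this study is the N75-P100 amplitude at 60 min after the induction of anesthesia", averaged over three occipital leads and both eyes. It is a raw value, not a change from baseline.
- **Test (Statistical analysis).** "The primary outcome (N75-P100 amplitude of FVEPs recorded 1 h after induction) will be analyzed using a superiority test". The decision rests on the "confidence interval for mean differences of N75-P100 amplitude between LD and HD groups", set against δ at one-sided 0.025. No covariate is named.
- **Sample size (Sample size calculation).** The inputs are the 60-minute pilot values only: "the amplitudes of the LD group and HD group were 3.43 ± 0.78 μV and 2.37 ± 0.80 μV, respectively". The margin is 20% of the HD amplitude, and no baseline correlation enters.
- **Baseline (Intervention).** "We will measure the baseline amplitude and latency of FVEPs 30 min after anesthesia induction under TIVA in both groups". Anaesthesia regimen gives one TIVA protocol for all patients, with ranges for propofol and remifentanil.
- **Use of the baseline (Study endpoints).** It appears in the secondary endpoints, for example the "N75-P100 amplitude decline rate compared to baseline measured under TIVA".
- **Imbalance (Statistical analysis).** "The absolute standard deviation (ASD) will be determined to identify any imbalance in baseline characteristics". No adjustment is said to follow from it.

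**The concern.** The baseline and the 60-minute value are the same quantity in the same patient, 30 minutes apart, recorded on the same system by the same neuroelectrophysiologist. If patients with a larger amplitude at baseline tend to have a larger one later, part of the spread in the 60-minute values can be predicted before the regimens diverge. A comparison that omits the baseline counts that part as noise.

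Two things are at stake in a trial with one confirmatory comparison and 35 patients per arm. The confidence interval is wider than it need be. And a chance difference in baseline amplitude carries over into the primary estimate in proportion to r, whereas the decline rates take the baseline into account. The two sets of results could then point in different directions, with no stated way to reconcile them.

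**Working it through.** **Inputs (Sample size calculation; Statistical analysis).** LD 3.43 (SD 0.78) μV, HD 2.37 (SD 0.80) μV, one-sided α = 0.025, power 0.80, 63 patients before dropout, 10% dropout, 1:1 allocation.

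**1. Effect beyond the margin**
- Difference: 3.43 − 2.37 = 1.06 μV
- Margin, taken as fixed: 0.20 × 2.37 = 0.474 μV
- Excess: 1.06 − 0.474 = 0.586 μV

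**2. The plan's own sample size.** A two-sample t calculation with no covariate needs 60 in total with pooled SD √[(0.78² + 0.80²)/2] = 0.790, or 62 with a common SD of 0.80. The stated 63 is within 1 of the latter, and 63/0.9 = 70. So the stated size is close to that of an unadjusted comparison.

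**3. Unadjusted precision and power with 31 and 32 analysed**
- SE = √(0.78²/31 + 0.80²/32) = 0.199 μV
- 95% CI half-width = 2.00 × 0.199 = 0.40 μV
- Power (noncentral t, 61 df, noncentrality 0.586/0.199 = 2.94) = 82.6%
- With 35 per arm, power is 86.4%

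**4. With the baseline as a covariate.** The adjusted SE is 0.199 × √(1 − r²), with 60 df. The article does not give r, so these values are assumptions:

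| r | 1 − r² | SE (μV) | 95% CI half-width (μV) | Power at 63 |
|---|---|---|---|---|
| none (unadjusted) | 1.00 | 0.199 | 0.40 | 82.6% |
| 0.3 | 0.91 | 0.190 | 0.38 | 85.9% |
| 0.5 | 0.75 | 0.172 | 0.34 | 91.7% |
| 0.7 | 0.51 | 0.142 | 0.28 | 98.2% |

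**5. Chance imbalance.** Assume that the baseline SD resembles the 60-minute SD, so that one SE of the baseline difference is also about 0.20 μV. If the baseline falls one SE against LD, the expected raw 60-minute difference shifts by r × 0.199, which is 0.06, 0.10 or 0.14 μV at r = 0.3, 0.5 or 0.7. Given that imbalance, the chance that the raw comparison succeeds is, by normal approximation,

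Φ[(0.586 − r × 0.199 − 1.96 × 0.199) / (0.199 × √(1 − r²))],

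or about 76%, 71% or 65%. The comparable figure with no imbalance and no adjustment is 83.7% (normal approximation; 82.6% by noncentral t). An equal imbalance in favour of LD would shift the estimate upward by the same amount. ANCOVA removes the shift in either direction.

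**The case against.** **The text is silent rather than wrong.** The article does not say t-test or unadjusted, and an adjusted mean difference would fit its decision rule. A separate analysis plan might name the covariate. That is fair, and it limits the point. Still, the article sets out the endpoint, the effect measure, the decision rule and the sizing, all without the baseline, and nothing in it says that adjustment will follow.

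**No harm appears on the trial's own inputs.** A reader might infer that the test is biased or the trial underpowered. The article does not support either reading. Under randomisation the unadjusted comparison is unbiased and controls type I error, chance imbalance is already reflected in its interval, and power exceeds 80% with a fixed margin.

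**The gain is assumed.** This stands. At r = 0.3 it is about 3 points of power and 0.02 μV of half-width. The Discussion cites work reporting unstable waveforms under TIVA, so a high r cannot be presumed.

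**The baseline is not a clean pre-randomisation measurement.** A reader might take the TIVA phase as identical in every patient. Anaesthesia regimen gives ranges for propofol and remifentanil. Under Randomization and blinding, the attending anaesthesiologist opens the envelope once the patient is in the operating room, so drug delivery before the baseline is in the hands of someone who knows the arm. This caveat stands and must be stated. In favour of the covariate, both arms follow the same TIVA protocol at that point and the neuroelectrophysiologist is blinded. Remedy also anticipates failed recordings, so not every patient need have a baseline.

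**The baseline is already used.** It would be too strong to say that the trial ignores it, since the decline and prolongation rates depend on it. Those are secondary and are different estimands, and ANCOVA would not guarantee that they agree with the primary result.

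**Conclusion.** The point holds as one of efficiency and robustness. The primary comparison is described without a baseline term although a suitable measurement is already collected. The unadjusted test remains valid and meets the planned power: 82.6% against 80% with 63 analysed.

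Adjustment would bring power to about 86%, 92% or 98% and the half-width from 0.40 to 0.38, 0.34 or 0.28 μV at r = 0.3, 0.5 or 0.7. These figures rest on the pilot means and SDs, a margin fixed at 0.474 μV, 31 and 32 patients analysed, and an assumed r. Any material correlation gives a gain. With r near zero, the cost is one degree of freedom.

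**What to change.** Before unblinding, prespecify the primary analysis as ANCOVA of the 60-minute N75-P100 amplitude on arm and TIVA baseline N75-P100 amplitude, on the original scale. Compare the confidence interval of the adjusted LD minus HD difference with the existing margin, and keep the unadjusted comparison as a sensitivity analysis.

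Add that the baseline is recorded after the envelope is opened but before the regimens diverge, by a blinded neuroelectrophysiologist. Report baseline amplitude and TIVA drug levels by arm to support its use as a covariate.

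No new data are needed. The cost is one degree of freedom and a documented amendment: under Ethics and dissemination, significant changes to analyses go to the Ethics Committee and the trial registry. A log-scale analysis with a ratio margin is optional and not part of this fix. It would change the decision rule, and its power has not been calculated here.

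### Six continuous secondary outcomes are assigned χ²/Fisher tests, and the exclusion of patients without FVEP data conflicts with the success-rate denominator and overlaps two unranked imputation rules

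*Protocol article*

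**What the plan says.** **Tests.** The Statistical analysis section of the protocol article states that χ² or Fisher's "exact tests will be performed for categorical variables including N75-P100 amplitude decline rate". The list goes on to the P100-N145 decline rate and the P100 prolongation rate, and ends with "success rate of FVEP monitoring, FVEP stacking satisfaction, adverse events related to FVEP monitoring, and recovery quality". Only anaesthetic and vasoactive drug consumption is given a t-test or Wilcoxon test.

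**Definitions.** Study endpoints introduces the first of these outcomes as "N75-P100 amplitude decline rate compared to baseline measured under TIVA, calculated by the formula", followed by (TIVA value − 60-min value)/TIVA value × 100%. The other two rates have the same form. Recovery quality includes respiratory recovery, eye-opening and extubation times; for example, "Extubation time is defined as the time from the cessation of anesthesia" to removal of the tube. It also includes agitation and Ramsay scores.

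**Lost recordings.** Statistical analysis says that patients who yield no available FVEP data, or who leave the study, "will be considered to have failed HD/LD and will be excluded from any form of analysis". The next sentence says that for missing data "the last observation and the worst-case imputation scenarios will be used as the main interpolation method". Under Remedy, "if the FVEPs fail to record or the surgery is suspended, the patients will remain in the study". Study endpoints defines the success rate as eyes with a satisfactory waveform over all monitored eyes.

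**The concern.** The first problem is one of type. A percentage change and a time in minutes are continuous, and a χ² or Fisher test needs categories that the article does not supply. If the text is followed, someone must later choose a cut-off for each of six outcomes. That costs power and leaves the choice open. The N75-P100 decline matters most here, because it is the baseline-referenced counterpart of the primary amplitude.

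The second problem concerns a patient who has a 30-min TIVA value but no 60-min waveform. Exclusion, last observation and worst case can each be read as applying, and no order is stated. Last observation and worst case pull in opposite directions. The same sentences govern the primary amplitude. Literal exclusion would also drop the very failures that the success rate is meant to count.

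**Working it through.** **The plan's own figure.** Sample size calculation gives 3.43 (SD 0.78) μV for LD and 2.37 (SD 0.80) μV for HD, with a margin of 20% of the HD value: 0.2 × 2.37 = 0.474 μV. The effect net of margin is 1.06 − 0.474 = 0.586 μV. With one-sided α 0.025, 80% power and SD 0.80, a t-test needs 31 per arm, or 62 in total, against 63 stated; 63/0.9 = 70. The plan's size is reproduced to within one patient and is not in dispute.

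**Cost of dichotomising.** Inputs: 35 per arm and two-sided 0.05 (both stated), with a normal outcome and equal SDs (assumed).
- A t-test has 80% power at a standardised difference of d = 0.679.
- Cutting at c turns this into event rates 1 − Φ(c) and 1 − Φ(c − d). Exact binomial summation gives:

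| Cut | Event rates | χ² (uncorrected) | Fisher |
|---|---|---|---|
| at one arm's mean | 50% v 75% | 0.595 | 0.504 |
| midway between the means | 37% v 63% | 0.588 | 0.493 |

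No cut does materially better than the first row. Cuts well off centre fall below 50% (χ²) and 40% (Fisher).

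**Lost waveforms: decline rate.** The Intervention section has two measurement times: the TIVA baseline at 30 min, and then "We will measure the amplitude and latency of FVEPs 60 min after anesthesia induction in LD or HD group". For a waveform wholly lost at 60 min, the last observation is therefore the TIVA value, which gives a decline of 0%. Worst case is 0 μV, a decline of 100%. With k of 35 patients lost in both eyes and a mean decline of d% in the rest:
- exclusion: d
- last observation: d(35 − k)/35
- worst case: [d(35 − k) + 100k]/35
- gap between the two imputations: 100k/35, whatever d is

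**Success rate.** If all k losses are in HD and affect both eyes, HD success is (70 − 2k)/70 with failures counted, and 100% with those patients excluded.

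**Primary outcome.** Using the pilot means, with T the TIVA value carried forward (not in the documents; assumed 2.37 to 4.0 μV):
- exclusion: 3.43 − 2.37 = 1.06
- worst case: 3.43 − 2.37(35 − k)/35
- last observation: 3.43 − [2.37(35 − k) + Tk]/35

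| HD losses k | Gap in mean decline (points) | HD success, failures counted | LD−HD, worst case (μV) | LD−HD, last observation (μV) |
|---|---|---|---|---|
| 1 | 2.9 | 97.1% | 1.13 | 1.01–1.06 |
| 3 | 8.6 | 91.4% | 1.26 | 0.92–1.06 |
| 4 | 11.4 | 88.6% | 1.33 | 0.87–1.06 |

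**How many losses?** The article's only figures are 100% monitoring success in the earlier sevoflurane study (0 losses), that study's 1.7% dropout (35 × 0.017 = 0.6 per arm) and the planned 10% (35 × 0.10 = 3.5 per arm).

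**The case against.** **On the tests.** Only secondary outcomes are affected. The categorical label may be loose wording, or a responder cut may have been meant: Background cites a 20% fall from baseline as a warning value. A missing cut-off alone could be left to an analysis plan. What stands is that the article states the test and the variable type, and both contradict its own definitions. The 20% value is tied to no endpoint and would not cover latency or recovery times. The only cut-off within recovery quality is for the Ramsay score. χ²/Fisher suits the success rate, stacking satisfaction and adverse events.

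A reader might infer that the stated test could never detect anything. With 70 distinct percentages it always returns χ² = 70 on 69 df, P = 0.44. That describes an analysis no statistician would run, so the realistic loss is the one from dichotomising.

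**On lost waveforms.** A narrower reading exists. The intention-to-treat definition refers to completed FVEP data, so patients without any may never enter the analysis set, leaving imputation for other gaps. Last observation has an ordinary use for the agitation and sedation scores, which are repeated up to 60 min after awakening. The Remedy sentence concerns trial conduct and does not strictly contradict exclusion from analysis. A patient who loses one eye still has data, so that failure stays in the denominator. All of this has force, but the article does not state the narrower scope. Even that reading conflicts with the success-rate denominator when both eyes fail.

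A reader might also infer that the primary result will be biased. The documents do not show this. Losses may be nil, and the figures above are point estimates that all exceed 0.474 μV. Nor does the text make 0 μV the obvious main analysis: that score favours LD if losses fall mainly in HD.

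**Conclusion.** The point holds in two parts.

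1. The test assigned to six continuous secondary outcomes is wrong as written. If it were carried out by dichotomising, power would fall from 80% to at most about 60% (χ²) or 50% (Fisher), assuming normal outcomes and 35 per arm.

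2. The exclusion sentence, read literally, contradicts the success-rate definition for patients whose recordings fail in both eyes. It also overlaps two unranked imputation rules. One of them would record a lost 60-min signal as no decline at all.

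The second part reaches the primary outcome only if waveforms are lost, and that number is unknown. The reassuring figures come from a study of 0.5 MAC sevoflurane with propofol against TIVA. HD here uses 0.7–1.0 MAC desflurane without propofol, so they may not transfer, but they do not show that losses will be common. This should be corrected; it does not invalidate the trial.

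**What to change.** - Analyse the two decline rates, the prolongation rate and the three recovery times as continuous, using the t-test/Wilcoxon rule already written for drug consumption. Any responder cut-off should be an additional summary, labelled as such.
- Restrict the exclusion so that failed recordings stay in the success-rate denominator as failures.
- Do not carry the TIVA value forward for a waveform lost at 60 min.
- Name one main handling rule for lost waveforms before unblinding. Report complete-case and worst-case (0 μV, 100% decline) results as sensitivity analyses, and say that worst case favours LD if losses occur mainly in HD. List losses by arm and cause.

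No new data or patients are needed: both measurements, the ERG check and the case report form entry for failed recordings are already planned. The cost is a dated clarification. Recruitment began in July 2022 and completion was estimated for June 2024, so it must be labelled as made during the trial and made before anyone sees results by arm.
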